### Data analysis

The SPSS 23.0 statistical software will be used for the data analysis. All the statistical hypotheses will be tested by two-side test, with statistically significant test level set at 0.05 and the confidence interval estimation to 95%.

The aim of our study is to evaluate the effects of the treatments in the various patient groups on the primary and secondary outcomes. Descriptive analysis of the data will allow us to identify the characteristics of the groups. Comparison of demographic and clinical characteristics of the groups will be performed using one-way ANOVA for continuous variables and the Chi-square test for categorical variables. Considering the crossover and longitudinal aspects, primary analyses will focus on behavioural changes at group level, comparing the treatments. Moreover, at the individual level, we will analyse the differences between pre-treatments and post treatments data.

As for the primary outcomes, we will measure the effects of the intervention on the following measures (two neurophysiological and two clinical and behavioral): (i) power spectra of frequency band extracted from the EEG recordings; (ii) auditory evoked responses, extracted from the EEG recordings; (iii) behavioural responses of DOC patients, measured through CRS-R.

Baseline characteristics and carryover effect will be analysed between the three sequences using ANOVA and chi-square test. By including the order of intervention as a covariate, we aim to determine whether the sequence in which participants receive the interventions impacts the observed outcomes. To assess the presence and magnitude of the washout effect, we plan to incorporate appropriate statistical methods into our analysis, such as comparing outcomes during the washout period to those observed during active treatment phases. To this end, we will use repeated measures ANOVA considering time (before, during, and after the washout) as the independent variable, with behavioral measurements as the dependent variables.

For the secondary outcome we will measure the effects of the treatments on caregivers’ depression, anxiety, psychophysiological symptoms, grief, strain and quality of life in order to evaluate the effectiveness in reducing the caregiver’s burden and psychological distress. Repeated-measures analysis of variance, as well as post-hoc paired *t*-tests will be conducted to assess the effects of the treatments over time on N1, P1, and P2 amplitudes and latencies, as well as level of consciousness. All these primary outcome variables will be analysed separately, using parametric or non-parametric tests for continuous and categorical variables respectively.

For the behavioural outcome, we expect an improvement of level of consciousness, as measured by CRS-R.

For the caregiver’s burden, we expect a positive effect of this new treatment protocol on caregiver’s wellbeing, with a decrease of psychological distress.

For neurophysiological outcome measures, we expect to obtain in DOC patients an increased EEG power spectrum in slow frequency bands, following a previous study [67] showing a generalized slowing in the theta or delta range associated with a significantly diminished α power. Power spectrum analysis is one of the standard methods used for quantification of the EEG. The power spectrum, namely the power spectral density, reflects the ‘frequency content’ of the signal or the distribution of signal power over frequency [68].

For the computation of the auditory evoked responses, the average EEG will be measured time-locked to the sound onset events in the music stimuli, after rejecting any residual noise exceeding 100 μV. P1 (fronto-central positive potential with ~50 ms latency), N1 (fronto-central negative potential with ~100 ms latency), and P2 (fronto-central positive potential with ~200 ms latency) amplitudes and latencies will be measured at the Fz and Cz electrodes [69], and compared pre- and post- intervention.

To reach the goal of obtaining the above-described neurophysiological outcome measures, we will first pre-process the EEG data as follows. Data will be filtered to remove low frequencies not originating from the brain and to control for interference of the electric current, by means of a generic FIR filter, set up as a bandpass filter, with low cut-off at 0.5 Hz and high cut-off at 45 Hz (because of 50 Hz power line noise). Cerebral signals contaminated by artifacts will be identified and removed. Moreover, independent component analysis (ICA) will be performed. ICA algorithms will be used to detect and isolate artifacts, such as eye blinks, eye saccades, hearth, muscle, line noise, channel noise and others. In this way, the original signal will be decomposed into independent components: we will individuate and discard the components that picked up the artifacts activities and reconstruct a clear signal by using only the remaining components [70]. Further pre-processing steps will include epoch extraction, baseline removal, resampling, re-referencing to low temporal electrodes, and filtering.

To investigate whether slow neural oscillations are reduced and fast neural oscillations are increased post-treatment, the continuous EEG will first be divided into 2-seconds segments, transformed into the frequency domain with fast Fourier transform, inspected for myogenic artifact segments that will be rejected, and then averaged across the segments [71]. Any further exploratory analyses will be specified in the future publication of the findings of this study. Missing data will be treated according to Molenberghs et al. [72].

We will evaluate the music and electrical intervention effects on power spectra of frequency bands measuring EEG at rest and during music listening at T0 (pre-intervention), T1 (post-intervention) and T2 (post-placebo). To this end, we will compare the power spectra between rest and music conditions and across time. The ratio of fast (8–30 Hz, alpha and beta) to slow (2–8 Hz, delta and theta) oscillation amplitude at the midline electrodes (Fz, Cz, Pz, Oz) will be measured [70] and compared pre- and post- intervention using t-tests with cluster-based corrections of the multiple comparison problem. In the case of non-normal distributions, there will be applied mixed-effect ANOVAs or non-parametric equivalents to the parametric tests.

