The outcome measures will be clinical, namely based on the neurologist’s observations of clinical improvement and responsiveness, measured through specific scales as well as neurophysiologically. For the latter, continuous EEG is expected to display a decrease of power spectra of slow frequency bands (delta-theta) and an increase in power for faster frequency bands (alpha, beta, gamma). We also expect to evaluate residual memory and learning processes in DOC patients by measuring a higher EEG N100 component amplitude after compared to before treatment. Also, amplitudes of the later-stage auditory P2 and latencies of the N100 and P2 will be explored. More broadly, the present intervention combining music exposure with electric neuromodulation is expected to produce increased evoked responses indexed in EEG measures.

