### Neurophysiological, neuropsychological and clinical primary outcomes

For obtaining the neurophysiological primary outcome measures, we will compute the power spectra of frequency bands from continuous EEG to assess the residual neuroplastic processes existing in DOC state, and we will then evaluate the putative modulation of these processes by the combined intervention of music and brain stimulation in a randomized cross-over design. EEG data will be acquired using a Galileo Mizar Plus medical device including 26 monopolar electrode channels, 16 bipolar electrode channels and 10 additional channels used for EEG recordings.

For the EEG measures, we will use the following paradigms:

Rest for 10 minutes with annotation on whether patients keep eyes open or closed for measuring the power spectra of frequency bands from the continuous EEG.Free listening to the morning musical playlist as used in the music stimulation condition for measuring the power spectra of frequency bands and the evoked N100 responses from the continuous EEG.

For assessing the clinical conditions of DOC patients, the following scales will be used.

Glasgow Outcome Scale–Extended (GOS-E) [53]: A global scale for functional outcome that rates patient status in eight categories according to the disability.Coma Recovery Scale—Revised (CRS-R) [54]: A tool which includes the current diagnostic criteria for coma, vegetative state, and the MCS, and allows the patient to be assigned to the most appropriate diagnostic category.Disability Rating Scale (DRS) [55]: A scale that evaluates the functional changes in a rehabilitation setting. The DR Scale consists of 8 items divided into 4 categories: Arousal and awareness; cognitive ability to handle self-care functions; physical dependence upon others; psychosocial adaptability for work, housework, or school.Rancho Levels of Cognitive Functioning (LCF) [56]: A scale that assesses cognitive functioning in post-coma patients, classifying them in one of eight level: No response; Generalized; Localized; Confused-agitated; Confused, inappropriate, non-agitated; Confused-appropriate; Automatic-appropriate; Purposeful-appropriate.

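### The primary outcome set differs between sections and its variables are tested separately at 0.05, so the chance of a false positive is about 13–19% for three to four outcomes; one sentence also reverses the expected slow-band change

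*Protocol article*

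**What the plan says.** All references are to the protocol article.

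- **Number.** Data analysis announces "two neurophysiological and two clinical and behavioral" primary measures. The list that follows has three items: EEG power spectra, auditory evoked responses, and "iii) behavioural responses of DOC patients, measured through CRS-R".
- **Clinical membership.** The section whose heading names the primary outcomes says "For assessing the clinical conditions of DOC patients, the following scales will be used" and gives GOS-E, CRS-R, DRS and LCF. The Abstract gives an open list, with the CRS-R as an example, plus EEG.
- **EEG membership.** The primary-outcomes section names power spectra and the N100. Data analysis later takes N1, P1 and P2 amplitudes and latencies together with level of consciousness and adds: "All these primary outcome variables will be analysed separately". The Introduction states an expectation for N100 amplitude only, leaves P2 amplitude and the N100 and P2 latencies to exploration, and does not mention P1.
- **Testing.** "All the statistical hypotheses will be tested by two-side test", "with statistically significant test level set at 0.05". The one multiplicity correction stated is cluster-based and attached to the t-tests of the fast/slow EEG ratio.
- **Direction.** Among the expected results, Data analysis says "we expect to obtain in DOC patients an increased EEG power spectrum in slow frequency bands". The Introduction says "continuous EEG is expected to display a decrease of power spectra of slow frequency bands (delta-theta". The Discussion, and a later paragraph of Data analysis on neural oscillations, also expect slow activity to fall and fast activity to rise.

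**The concern.** A reader cannot tell which variables are primary. The second clinical primary measure is announced but not named, and three other scales under the primary heading could fill the place after the data are seen. The same evoked-response variables are exploratory in one section and primary in another. No section ranks the outcomes or says how many must succeed.

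With separate tests at 0.05 and no correction across outcomes, the overall false-positive rate exceeds 5%. Its value cannot be fixed while the set is open. The contradictory statement about slow-band power also leaves the EEG hypothesis unclear on a two-sided test.

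**Working it through.** **1. The sections side by side**

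| Section | Clinical | EEG |
|---|---|---|
| Abstract, Methods | open list, CRS-R as example | EEG, unspecified |
| Primary outcomes section | GOS-E, CRS-R, DRS, LCF | power spectra, N100 |
| Data analysis, announced | two | two |
| Data analysis, listed | CRS-R only | power spectra, evoked responses |
| Data analysis, later | level of consciousness | P1, N1, P2: amplitude and latency |
| Introduction | neurologist's observation and scales | power; N100 amplitude; P2 and latencies exploratory |

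These versions cannot all hold.

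**2. The plan's own figure.** Sample size determination gives N = 30 for 80% power at f = 0.30 and alpha 0.05, with three groups and three time points. For the group-by-time interaction, λ = N·m·f²/(1 − ρ), where m is the number of measurements. The correlation ρ is not stated, so it is assumed here.

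- m = 2, ρ = 0.5: λ = 30 × 2 × 0.09 / 0.5 = 10.8, power 0.800.
- m = 3, ρ = 0.5: λ = 30 × 3 × 0.09 / 0.5 = 16.2 on 4 and 54 degrees of freedom, power 0.887. Power is 0.80 at ρ of about 0.38.

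So N = 30 can be reproduced, but for one test at an unadjusted 0.05.

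**3. Chance of at least one false positive.** For k independent tests at 0.05 it is 1 − 0.95^k. The second column is a simulation of k two-sided z-tests with a common correlation of 0.5, which is an assumption. Each variable counts as one test; the planned post-hoc paired t-tests are not counted.

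| Reading | k | Independent | Correlation 0.5 |
|---|---|---|---|
| Outcomes as listed | 3 | 14.3% | 12.6% |
| Outcomes as announced | 4 | 18.5% | 15.5% |
| 3 components × 2 (amplitude, latency) = 6, plus EEG ratio and CRS-R | 8 | 33.7% | 25.2% |
| As above, evoked responses tested at both Fz and Cz: 12 + 1 + 1 | 14 | 51.2% | 34.8% |

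The last row assumes a separate test per electrode. The article says only that the components are measured at both electrodes. The cluster-based correction is respected throughout, because the ratio counts as one test.

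**4. Price of control.** With m = 3 and ρ = 0.5, splitting alpha equally gives:

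- three outcomes, 0.05/3 = 0.0167 each: power 0.772 at N = 30; 80% needs N = 33 in equal groups;
- four outcomes, 0.05/4 = 0.0125 each: power 0.737; 80% needs N = 36.

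Holm is never less powerful than this equal split.

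**The case against.** **The analysis plan may settle it.** It is not shown, and an article often leaves the rule across outcomes to it. The remark about separate analysis continues into the choice of parametric or non-parametric tests, and neither it nor the general 0.05 level rules out an adjustment. This stands in part: a missing multiplicity rule alone would be weak ground. But the article itself prints conflicting counts and memberships, and an adjustment cannot be defined over a set that is not fixed.

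**P1, N1 and P2 are components of a listed item.** This also stands. Against the list in Data analysis they are operational detail. The conflict is with the Introduction, which treats P2 and the latencies as exploratory, and with the primary-outcomes section, which names only the N100.

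**A reader might infer that a false positive is likely.** The figures do not support that. The rate passes 50% only from 14 independent tests. That count needs the per-electrode split, and independence is implausible for components of one waveform at two midline sites.

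**A reader might infer that opposite EEG results would both count as success.** The article sets no such criterion. The deviant sentence cites a study showing generalised slowing with reduced alpha power, and the Introduction describes resting EEG in DOC in similar terms. It is plausibly a misplaced description of untreated patients. It still stands among the expected results and needs correcting.

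**A reader might conclude that the CRS-R must be the sole primary outcome.** That goes too far. Residual neuroplasticity is the first objective in the Abstract. The Discussion also says assessors cannot be blinded (against Experimental design and procedures, which says they are), so resting everything on an examiner-rated scale is debatable.

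**Conclusion.** The point holds in this form: the primary set is inconsistent in number and membership, the stated testing does not control error across it, and one sentence contradicts the expected slow-band direction. Followed as written, the chance of at least one false positive is about 13–14% for the three listed outcomes and 15–19% for four. It is about 25–34% if six evoked-response variables, the EEG ratio and the CRS-R are each tested. The ranges run from an assumed correlation of 0.5 to independence; higher values need per-electrode testing, which the article does not state. Every reading exceeds the nominal 5%. The correction inside the fast/slow-ratio tests does not change this, because it covers neither the CRS-R, the other scales nor the evoked responses. This should be put right before analysis.

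**What to change.** Before any outcome data are analysed:

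1. Fix one closed primary set, identical in the Abstract, the primary-outcomes section and Data analysis. Use the three listed outcomes with one named variable each: CRS-R total, resting fast/slow ratio, and N1 amplitude with its electrode or electrode average named.
2. Control the error across the three with Holm. Alternatively, test in a fixed order with the CRS-R first, each at 0.05, stopping at the first non-significant result; this matches the stated focus of the primary analyses on behavioural change.
3. Label GOS-E, DRS, LCF, P1, P2 and the latencies secondary or exploratory, and correct the announced count to one clinical measure.
4. Change the slow-band expectation in Data analysis to a decrease, or mark the sentence as describing untreated DOC EEG.

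The cost is wording, with no new data or visits. Holm lowers power per outcome somewhat: from 0.887 to no lower than 0.772 under the assumptions above. The fixed order avoids that loss for the CRS-R but makes the EEG outcomes depend on it. The demoted measures carry less formal weight.

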### Sample size determination

The effect size to be expected is uncertain as no study so far has implemented a combined intervention of music and electrical stimulation in DOC patients. We assume it to be in the medium-to large range (i.e., Cohen’s d between 0.5 and 0.8). We aim to achieve 80% power (*f* = 0.30) in a repeated-measures analysis of variance (*a* = 0.05, power (1-b) = 0.80) with condition as between-subject factor (tES combined with music stimulation vs. sham stimulation, and noise vs. music stimulation and sham stimulation), and time (pre-intervention, post-intervention and post-placebo), as within-subject factor. Power calculations (using G* Power 3) indicate that a valid sample size of *n* = 10 per group will result in 80% statistical power if the effect is *d* = 0.68, which is in the medium-to-large range. This results in a total sample size of *n* = 30.

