### Experimental design and procedures

The experimental paradigm is one of the main strengths of the study, as a randomized cross-over design will be used in this trial, including a treatment condition with electric brain stimulation combined with music listening and a placebo condition with sham brain stimulation combined with noise listening. The randomization of the participants to be included in each group will be done using the software “Research Randomizer” (www.randomizer.org). The randomization procedure will be performed by an independent researcher unrelated to the study. The randomization file will be saved in a password-protected online database. This independent researcher will enrol participants and will assign the patients to intervention groups. Both patients and examiner will be fully blinded.

Assessment times of outcome measures will be conducted at admission (T_0_), after the first weeks of post-intervention or post-placebo (T_1_), and after the second two weeks of post-intervention or post-placebo (T_2_) (Fig 1). Patients will be randomized into three groups depending on the order of the stimulation or placebo conditions:

Stimulation-Placebo: Patients receiving tES combined with music stimulation for 2 weeks, 1 week of wash out, then sham stimulation combined with noise (placebo) for other 2 weeks.Placebo-stimulation (combined tES and music): Patients receiving sham stimulation and noise (placebo) for the first 2 weeks, then 1 week wash out, and finally tES and music stimulation for other 2 weeks.Music-placebo: Patients receiving music stimulation and sham stimulation for 2 weeks, 1 week of wash out, then sham stimulation and noise (placebo) for another 2 weeks.

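### Order of intervention as a covariate duplicates the randomised group where group or patient is in the model, and as a patient-level term it leaves any period effect in the within-patient contrasts; period should take its place

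*Protocol article*

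**What the plan says.** Experimental design and procedures: "Patients will be randomized into three groups depending on the order of the stimulation or placebo conditions". The groups are:

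- Group 1, combination then placebo: "Patients receiving tES combined with music stimulation for 2 weeks, 1 week of wash out", followed by two weeks of placebo.
- Group 2, placebo then combination: "Patients receiving sham stimulation and noise (placebo) for the first 2 weeks", then a one-week washout and the combination.
- Group 3, music then placebo: "Patients receiving music stimulation and sham stimulation for 2 weeks, 1 week of wash out", followed by placebo. No group receives placebo and then music.

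Sample size determination describes a repeated-measures ANOVA and lists treatments, not sequences, as its between-patient factor: "with condition as between-subject factor (tES combined with music stimulation vs. sham stimulation, and noise vs. music stimulation and sham stimulation". The within-patient factor is labelled by condition and not by calendar period: "and time (pre-intervention, post-intervention and post-placebo), as within-subject factor". The section plans 10 patients per group, 30 in all.

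Data analysis compares baseline characteristics and carryover across the three sequences, then adds: "By including the order of intervention as a covariate, we aim to determine whether the sequence in which participants receive the interventions impacts" outcomes. It names no term for first versus second treatment period. It also treats T1 as the visit after intervention and T2 as the visit after placebo, whereas the design section lets either visit follow either condition, as it must for group 2.

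**The concern.** A patient's order is fixed at randomisation and is already known from the group. A covariate that repeats a factor in the model cannot be tested beside it. A covariate that is constant within a patient also cannot alter a contrast between that patient's own two treatment periods.

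The quantity that can distort those contrasts is period, meaning change between the first and second treatment blocks for reasons other than the study treatment. Such change is plausible here. Each patient is followed for about five weeks (two, one and two), all receive daily physiotherapy, and most receive drugs meant to raise the level of consciousness. Two of the three groups receive active treatment first, and music is never given second. At stake are the within-patient comparisons of active treatment with placebo, such as the planned post-hoc paired t-tests where they make that comparison, and above all those for music.

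**Working it through.** The plan gives no figure for this point. The inputs are the three sequences (Experimental design and procedures) and 10 patients per group (Sample size determination). The sample size itself is not questioned here.

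**1. Does order add anything to the model?** Code order as 1 for active-first (groups 1 and 3) and 0 for placebo-first (group 2). Then order = 1 - (indicator of group 2). Ranks of the design matrix with 10/10/10 patients:

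| Model | Without order | With order | With period instead |
|---|---|---|---|
| Intercept + three-level group | 3 | 3 | - |
| Group x time | 9 | 9 (also with order x time) | - |
| Patient + treatment (combination, music, placebo) | 32 | 32 | 33 |
| Intercept + active type (combination or music) | 2 | 3 | - |

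In the first three rows order has zero degrees of freedom. In the last row it has one.

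**2. Bias from a period effect.** Let delta be the second-period level minus the first-period level when no treatment has any effect. The mean within-patient difference, active minus placebo, is then:

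- Group 1 (active first): d1 = 0 - delta = -delta
- Group 2 (active second): d2 = delta - 0 = +delta
- Group 3 (active first): d3 = 0 - delta = -delta

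Without a period term:

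- Combination, groups 1 and 2: (d1 + d2)/2 = 0
- Music, group 3: d3 = -1.0 delta
- Pooled active minus placebo: (10 d1 + 10 d2 + 10 d3)/30 = -delta/3 = -0.33 delta

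An order main effect adds the same constant to both of a patient's periods. It cancels from d1, d2 and d3, and all three results stay as they are.

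**3. With period in the model.** Groups 1 and 2 identify the period effect as (d2 - d1)/2 = (delta + delta)/2 = delta. Then:

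- Combination: (d1 + d2)/2 = 0, unchanged
- Music: d3 + (d2 - d1)/2 = -delta + delta = 0
- Pooled: [mean of d1 and d3, plus d2]/2 = (-delta + delta)/2 = 0

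**4. Range.** Delta is not in the documents, so these values are assumptions, in SD units:

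| Assumed delta | Music, order or no order | Pooled, order or no order | Either, with period |
|---|---|---|---|
| 0 | 0 | 0 | 0 |
| 0.25 | -0.25 | -0.08 | 0 |
| 0.50 | -0.50 | -0.17 | 0 |

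If patients improve over time, the bias works against active treatment. If they decline, the signs reverse.

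**5. Can order-by-treatment be fitted beside period?** In groups 1 and 2, code order as +1 (active first) or -1, treatment as +1/2 (active) or -1/2, and period as +1/2 (second) or -1/2. Then period = -(order x treatment) in all four cells. Patient + treatment with either term, or with both, has rank 22 (20 patients, one treatment term and one more), so the two terms are the same term.

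**6. Precision.** Let V be the variance of one within-patient difference, taken as equal across groups. Unadjusted music has variance V/10 = 0.10V. With period it is V/10 + (V/10 + V/10)/4 = 0.15V, so the standard error rises by a factor of sqrt(1.5) = 1.22. The combination estimate keeps its formula and its variance.

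**The case against.** The strongest objection is that the article does not write out the model. The Sample size section calls the between-patient factor condition and lists treatments, not sequences. If that factor separates only combination from music, order is not aliased (rank 2 to 3). A reader might infer that the covariate has zero degrees of freedom whatever the model; the text does not establish that, and this part of the objection stands. It does not rescue the covariate. As a main effect, order then compares patients' average levels, which period shifts equally in groups 1 and 2. Even with neither group nor patient terms, at an assumed within-patient correlation of 0.5, adding order moves the music bias only from -0.83 delta to -0.87 delta.

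If order were also crossed with treatment in an active-versus-placebo model, it would carry the period effect. The pooled bias would then be 0 with effect coding but +1.0 delta for the main term with 0/1 coding. The article states no such interaction.

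Three further points stand:

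- The plan offers order as a check on whether sequence matters. A reader might infer that it is meant to correct for period; the document does not say so.
- The primary analyses are described as comparing treatments at group level. A between-group comparison of change from T0 to T1 covers the same period in every group and has no period bias. The article does not explicitly plan a pooled active-versus-placebo contrast.
- The comparison across the three sequences already addresses order for the combination, through the group factor itself.

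**Conclusion.** The point holds in a limited form. With group or patient terms in the model, the order covariate is empty. Where order can be estimated, as a patient-level main effect it leaves the period effect in within-patient contrasts: -1.0 delta for music minus placebo and -0.33 delta for the pooled contrast, both 0 with period. These figures assume 10 patients per sequence, a period effect common to all sequences and no carryover. Delta itself is unknown and may be small.

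A reader might infer that the trial's treatment comparisons are biased throughout, or that adding period repairs the combination contrast. The documents support neither. The combination contrast from groups 1 and 2 is already unbiased while those groups are balanced, and between-group comparisons of change from T0 to T1 are unaffected. The exposure is in within-patient contrasts for music and in any contrast that pools the three groups.

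**What to change.** - Replace the order covariate with period (first or second) as a within-patient factor beside treatment received (combination, music, placebo). Code period by calendar block, so that group 2's T1 counts as first period and as placebo.
- Do not add a separate order-by-treatment term; in groups 1 and 2 it is the same as period.
- Assess carryover for the combination by comparing group 1 with group 2 between patients on the mean of T1 and T2, and state that power is low. At 10 per group, a two-sample t-test has power 0.30 for a difference of 0.68 SD, the plan's own effect size.
- State that order and carryover cannot be estimated for music alone, and that its period adjustment is borrowed from groups 1 and 2. The adjustment therefore assumes that they share its period effect and that carryover is absent.

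The cost is analysis wording and one degree of freedom, with no new data or visits. The adjusted music estimate also has the 1.22-fold larger standard error shown above.
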